**Urinary tract infection:**

The patient has at least **one** of the following signs or symptoms with no other recognized cause:

- Fever (>38°C)
- Urgency
- Frequency
- Dysuria or suprapubic tenderness

and the patient has a positive urine culture, that is, ≥ 105 microorganisms per cm3 of urine with no more than two species of microorganism.

The patient has at least **two** of the following signs or symptoms with no other recognized cause:

- Fever (>38°C)
- Urgency
- Frequency
- Dysuria or suprapubic tenderness

And at least **one** of the following:

- Positive dipstick for leukocyte esterase and/or nitrate
- Pyuria (urine specimen with ≥ 10 WBC/mm3 or ≥ 3 WBC/high power field of unspun urine)
- Organisms seen on Gram stain of unspun urine
- At least ***two***urine cultures with repeated isolation of the same uropathogen (gram-negative bacteria or *S. saprophyticus*) with ≥ 102 colonies/mL in nonvoided specimens
- ≤ 105 colonies/mL of a single uropathogen (gram-negative bacteria or *S. saprophyticus*) in a patient being treated with an effective antimicrobial agent for a urinary tract infection
- Physician diagnosis of a urinary tract infection
- Physician institutes appropriate therapy for a urinary tract infection

**Sinusitis:**

Sinusitis must meet at least one of the following criteria:

- Patient has organisms cultured from purulent material obtained from sinus cavity
- Patient has at least ***one***of the following signs or symptoms with no other recognized cause:
  - Fever (≥38°C)
  - Pain or tenderness over the involved sinus
  - headache, purulent exudate, or nasal obstruction
- *And* at least ***one***of the following**:**
  - Positive transillumination
  - Positive radiographic examination

**SIRS:**

Definition of sepsis according to the criteria of the ”Society of Critical Care Medicine Consensus Conference“ :

At least ***two*** of the following criteria must be fulfilled for the diagnosis of SIRS:

- Body core temperature > 38,0 °C or < 36,0 °C
- Heart rate: >90/min without ß-antagonism
- Or ***two*** of the following signs of respiratory failure:
  - Respiratory rate: < 20/min
  - Hyperventilation PaCO2 < 32mmHg in spontaneous breathing patients
  - paO2 < 70 mmHg (spontaneous breathing patients)
  - paO2/FiO2 < 175 (in mechanically ventilated patients and without medical history)
- WBC count: >12000/mm3 or <4000/mm3 or >10% immature forms

**Sepsis:**

- SIRS-Criteria (see above) are fulfilled
- Infection, documented or suspected

As the case may be

- An excessive activation of primarily protective defensive systems of the septic patient in terms of a host defense failure disease

**Severe Sepsis:**

Sepsis-Criteria and systemic toxicity or decreased organ perfusion **with two or more** characteristic signs:

- - Acute renal failure (Creatinine increase > 0.5 mg/dl or Oliguria < 0.5 ml*kg-1*h-1)
  - Increased plasma lactate (>1.8 mmol/l)
  - CI >4.0 l/min with SVR <800 dyn*s*cm-5
  - Metabolic acidosis (pH <7.3 or base deficite >5)
  - Arterial hypoxemia: PaO2 <75 mmHg (<10kPa)
  - Decrease of platelets within the last 24h with no other recognized cause (<100000/ml or decrease of more than 50% of the initial value)
  - Coagulation abnormalites within the last 24h with no other recognized cause (INR >1.5 or aPTT >1.2 * initial value)
  - Altered mental status with a sudden decrease of the Glascow-Coma-Scale

**Septic Shock:**

Signs of sepsis and refractory arterial hypotension despite adequate fluid resuscitation with decreased tissue perfusion or organ dysfunction

Hypotension is defined by at least one of the following characteristics:

- - Systolic blood pressure < 90 mmHg
  - Lasting decrease of blood pressure < 40 mmHg despite adequate fluid resuscitation without antihypertensive drugs
  - Therapy with vasopressors to maintain blood pressure < 90 mmHg

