| 4.Subject of the study and its aims  (Hypothesis divided into primary and secondary hypotheses) | Primary Hypothesis:  Compared to conventional therapy an intra-operative goal-directed haemodynamic management by monitoring with LiDCOrapid or oesophageal Doppler improves haemodynamics measured by stroke volume (SV) in patients undergoing elective liver resection.  Secondary hypothesis 1:  Compared to conventional therapy an intra-operative goal-directed haemodynamic management by monitoring with LiDCOrapid or oesophageal Doppler reduces the incidence of perioperative dysfunction (cerebral, pulmonary, renal, abdominal and cardiovascular), the amount of intraoperative blood loss and the postoperative incidence of infections and quality of life in patients undergoing elective liver resection.  Secondary hypothesis 2:  Compared to conventional therapy an intra-operative goal-directed haemodynamic management by monitoring with LiDCOrapid or oesophageal Doppler the postoperative liver function in patients undergoing elective liver resection.  Study groups:  The administration of the volume and catecholamine therapy is carried out by:  1.) Conventional standard therapy  2.) Goal-directed haemodynamic management by monitoring with oesophageal Doppler  3.) Goal-directed haemodynamic management by monitoring with LiDCOrapid  Primary outcome measure:  Stroke volume before intra-operative start of liver resection  Secondary outcome measures:   - Intra-operative and post-operative haemodynamic parameters - Intra-operative and post-operative blood loss - frequency of organ dysfunctions (cerebral, pulmonal, renal, abdominal, cardiovascular) - Post-operative liver function (LiMAx-test, ICG-Clearance, liver Doppler, laboratory tests: enzymatic and chemical parameters) - Peri-operative weight change - Post-operative incidence of infections - Satisfaction of the patients, the surgeons and anaesthetists - Time to fulfilling discharge criteria - Length of intensive care stay and hospital stay (LOS) - Quality of life measure (EQ-5D) - Laboratory tests: peri-operative endothelial and immunological alterations |

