**Appendix 4**

**Definition of infectious complications:**

For the diagnosis of an infection the following SOP from our hospital will be applied in accordance with the CDC criteria and ATS guidelines [15]:

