**Wound infection:**

**Superficial post-operative wound infection:**

Infection at the incision site within 30 days of operation which only involves the skin or subcutaneous tissues,

and one of the following criteria are met:

- Purulent discharge from the superficial incision
- Microbe isolated from culture of an aseptically obtained wound secretion or a tissue culture of the superficial incision

and one of the following signs:

- Pain
- Tenderness
- localised swelling
- Erythema or warmth
- The surgeon would open the superficial incision except that a **negative culture exists before the diagnostic decision**.

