**Deep post-operative wound infection:**

Infection within 30 days of operation. The infection appears to be associated with the operation and involves muscle tissue and fascial layers.

In addition to this one of the following criteria must be met:

- Purulent secretions from deep in the incision but not from an organ and/or body cavity
- Spontaneous drainage or deliberate surgical incision when the patient has at least one of the following symptoms:
- Fever (>38°C)
  - localised pain or tenderness
  - culture is confirmed negative
- An abscess or other sign of infection is evident from clinical, radiological or histopathological examinations or during re-operation
- diagnosis made by the surgeon

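### Three criteria in Appendix 4 (one for SIRS, two for septic shock) are printed the wrong way round, and the negative-culture lines for wound infection need reconciling

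*Protocol*

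**What the plan says.** Section 4 of the protocol includes the "postoperative incidence of infections" in secondary hypothesis 1 and lists it again among the secondary outcomes. Appendix 4 is the operative rule: "For the diagnosis of an infection the following SOP from our hospital will be applied".

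Five lines in that appendix matter here.

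- **SIRS.** One of the four criteria is met when two signs of respiratory failure are present. The first sign listed is "Respiratory rate: < 20/min". The next is hyperventilation with a PaCO2 below 32 mmHg.
- **Septic Shock, pressure fall.** Any one of three items establishes hypotension. The first is a systolic pressure below 90 mmHg. The second is "Lasting decrease of blood pressure < 40 mmHg despite adequate fluid resuscitation without antihypertensive drugs".
- **Septic Shock, vasopressors.** The third item is "Therapy with vasopressors to maintain blood pressure < 90 mmHg".
- **Deep post-operative wound infection.** A draining or surgically opened incision qualifies if at least one listed symptom is present. The list holds fever, localised pain or tenderness, and "culture is confirmed negative".
- **Superficial post-operative wound infection.** The last entry in the list of signs says that the surgeon would open the incision, except that a "negative culture exists before the diagnostic decision".

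Sepsis requires the SIRS criteria. Severe sepsis requires the sepsis criteria, and septic shock requires signs of sepsis.

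**The concern.** The SIRS and septic shock lines conflict with their neighbours. A low respiratory rate and hyperventilation point in opposite directions, yet both count towards respiratory failure. If a systolic pressure below 90 is the abnormal state, holding the pressure below 90 cannot be the aim of vasopressor therapy. A fall that counts only when it is small makes the milder event the qualifying one.

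The deep wound problem is different in kind: a finding that gives no support to infection sits among the findings that complete the diagnosis.

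What is at stake is how secondary outcomes are classified. An assessor who follows the text literally will place some patients in the wrong class. An assessor who follows the evident intention will not, and two assessors may choose differently. With 20 patients per group (section 14), a few reclassified patients can move a comparison. Section 15 also intends the results to lead to a later trial with a calculated sample size, so wrong event rates could carry forward.

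**Working it through.** The protocol states no figure to reproduce here, and section 14 says no sample size could be calculated. The check applies each rule as printed and with its direction reversed, and compares the classes.

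**1. SIRS, respiratory criterion**

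Inputs: the four respiratory signs and the need for two of them (Appendix 4, SIRS). Test values for the rate are 15 and 26 per minute. The other three signs are each present or absent, giving 2 × 2 × 2 × 2 = 16 combinations.

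- As printed: (rate < 20) + number of other signs ≥ 2.
- Reversed: (rate > 20) + number of other signs ≥ 2.

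Six of the 16 change class. At rate 15, three combinations count as printed but not when reversed. At rate 26, three count when reversed but not as printed. All six have exactly one other respiratory sign. With none, neither version reaches two; with two or more, both do.

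SIRS needs two of four criteria, so a changed respiratory criterion alters SIRS only if exactly one of temperature, heart rate and white cell count is met. That is 3 of the 8 patterns of those three. Overall, 6 × 3 = 18 of 16 × 8 = 128 patterns change SIRS status. These are counts of patterns, not probabilities. Some patterns cannot occur in one patient, because certain signs apply only to spontaneously breathing patients and one only to ventilated patients.

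**2. Septic shock, hypotension list**

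Assumption: all pressures are systolic (the second and third items do not say).

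- As printed: SBP < 90, or a fall between 0 and 40, or vasopressors with SBP < 90.
- Reversed: SBP < 90, or a fall above 40, or vasopressors with SBP ≥ 90.

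| SBP (mmHg) | Lasting fall (mmHg) | Vasopressors | As printed | Reversed |
|---|---|---|---|---|
| 105 | 0 | yes | no | yes |
| 105 | 10 | no | yes | no |
| 100 | 60 | no | no | yes |
| 100 | 60 | yes | no | yes |
| 105 | 25 | yes | yes | yes |
| 85 | 50 | yes | yes | yes |

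The errors go both ways. As printed, the vasopressor item adds no patient whom the SBP < 90 item has not already caught.

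**3. Deep wound infection**

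For a draining or opened incision, three findings can each complete the criterion: fever, pain or tenderness, negative culture. Of the 2 × 2 × 2 = 8 patterns, the culture line decides one: no fever, no pain or tenderness, culture negative. That patient counts as infected as printed.

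**4. Illustration of dilution (assumed figures)**

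The true event rates and the accuracy of classification are not in the documents. With true rate p, sensitivity se and specificity sp, the observed rate is q = p × se + (1 − p)(1 − sp). For p = 0.40 and 0.10, se = 0.8, sp = 0.9:

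- q1 = 0.32 + 0.06 = 0.38
- q2 = 0.08 + 0.09 = 0.17

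Approximate power, two-sided 5%, 20 per group, is Φ[(|q1 − q2| − 1.96 × SE0) / SE1], where SE0 uses the pooled rate and SE1 the separate rates.

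| Assumed true rates | se 1, sp 1 | se 0.8, sp 0.9 | se 0.6, sp 0.8 |
|---|---|---|---|
| 40% v 10% | 0.60 | 0.31 | 0.13 |
| 50% v 20% | 0.51 | 0.28 | 0.12 |

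This shows only the direction of the effect when the error is equal in both groups. It does not estimate what Appendix 4 would cause.

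**The case against.** The strongest reply is that these are wording slips whose intention is plain from the neighbouring lines, in exploratory outcomes of a 60-patient pilot. Most of that stands. The primary outcome is stroke volume. Section 15 treats all p values as exploratory. SIRS, sepsis and septic shock are not named individually in section 4, and none of the site-specific infection definitions uses SIRS. Sepsis also needs a documented or suspected infection, so a false SIRS does not create an infection. Plain intention does not cure the text, however, because Appendix 4 is the rule to be applied.

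A conversion fault is an unlikely explanation. Comparison signs print in the expected direction elsewhere in the appendix, and the culture lines are in words.

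Some stronger readings are tempting but not supported:

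- **Nearly every septic patient would count as septic shock.** The definition also requires hypotension that persists despite fluid, with decreased tissue perfusion or organ dysfunction. A large fall is missed only if the systolic pressure stays at or above 90 and no other item is met.
- **A negative culture should rule out deep infection, as it does for superficial infection.** The superficial line also sits inside a list of signs and is too garbled to serve as a model. The nesting of the deep list is uncertain in the text available. Deep infection can also be reached by other routes, including the surgeon's own diagnosis.
- **The platelet limit is a further error.** The line reads "Decrease of platelets within the last 24h with no other recognized cause (<100000/ml or decrease of more than 50" per cent. Dividing by 1000 gives 100 per mm3, but the white cell limits concern different cells, so calling it wrong needs outside knowledge. It is not an inversion either.
- **Unblinded assessors would fill the gap.** The protocol does not call the trial open-label. Sections 13 and 23 refer to unblinding, and section 19 separates study staff from treating doctors.

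**Conclusion.** The concern holds for three inverted thresholds, one in SIRS and two in Septic Shock, and for the negative-culture wording in the two wound definitions. The inversions show from the document's own lines, without any outside source.

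If the text is applied literally, SIRS, sepsis and septic shock can be misclassified in both directions. One narrow pattern of deep incision can be counted as infected on a negative culture alone. For the respiratory line, the effect is confined to patients with exactly one other respiratory sign, and SIRS status then changes only if exactly one other SIRS criterion is met. The finding that the vasopressor item adds no patient assumes that it refers to systolic pressure.

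How many patients this would affect cannot be derived from the documents. A reader might infer that the infection comparison as a whole is invalid. That does not follow: apart from deep wound infection, and the unclear line for superficial infection, the site-specific counts are not touched by these lines. Severity is moderate to minor.

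**What to change.** Before outcomes are classified, check Appendix 4 against the hospital SOP and the consensus definition that it cites, and then:

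1. Correct the direction of three outcome-classification thresholds: the respiratory rate in SIRS, and the pressure fall and vasopressor items in Septic Shock. State whether the last two refer to systolic pressure.
2. Reconcile the negative-culture wording in the superficial and deep wound definitions with the SOP, so that its role in each is unambiguous. The documents do not settle what that role is, so the source should decide it.
3. Carry the corrected wording into the case report form.
4. Reclassify any patient already assessed from the recorded data, and document that this was done.

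These changes concern how outcomes are classified, not how patients are treated. The cost is an edit to one appendix and to the case report form, plus any reclassification; no new data need be collected if the underlying values are on record.

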**Definition of ARDS according to the american-european consensus-conference (AECC) :**

- acute onset of the disease
- paO2/FiO2 (Horovitz)-Index < 200 mmHg independent of the applied PEEP
- bilaterale infiltrates in a.p.-x-ray of the thorax
- PCWP < 18 mmHg  exclusion of a cardial edema, where required using an esophageal echocardiography

**Lung Injury Score (LIS) by Murray (1988):**

- Goal of the score is the rating of the pulmonary function, i.e. in ARDS
- 4 criteria:
  - X-ray of the lungs
  - Number of quadrants showing alveolar consolidation on chest X-ray
    - 0 – 4 quadrants
  - Hypoxemia according to the Horovitz-Index:
    - > 300 mmHg
    - 225 – 299 mmHg
    - 175 – 224 mmHg
    - 100 – 174 mmHg
    - < 100 mmHg
  - PEEP:
    - < 5 cm H2O
    - 6 – 8 H2O
    - 9 – 11 H2O
    - 12 – 14 H2O
    - > 15 H2O
  - Compliance:
    - > 80 ml/cm H2O
    - 60 – 79 ml/cm H2O
    - 40 – 59 ml/cm H2O
    - 20 – 39 ml/cm H2O
    - < 19 ml/cm H2O

**Points:**

0 – 4

0

1

2

3

4

0

1

2

3

4

0

1

2

3

4

**Assessment:**

The sum oft he values divided by the number of groups evaluated:

Points:

0 No lung injury

0,1 – 2,5 slight or moderate lung injury

>2,5 severe lung injury

**Appendix 5**

**Definition of the RIFLE-Criteria of acute renal failure :**

According to: Bellomo R. et al., Critical Care 2004, 8:R204-R212

**Appendix 6**

**Definition of the Delirium Detection Score, the Nursing Delirium Rating Scale and the CAM-ICU for the detection of delirant states:**

**Delirium Detection Score = DDS**

| **Orientation** | # 0: Orientated to time, place and personal  identity, able to concentrate  # 1: Not sure about time and/or place, not able to  concentrate  # 4: Not orientated to time and/or place  # 7: Not orientated to time, place, and personal  identity |
| --- | --- |
| **Hallucinations** | # 0: Normal activity  # 1: Mild hallucinations at times  # 4: Permanent mild to moderate hallucinations  # 7: Permanent severe hallucinations |
| **Agitation** | # 0: Normal activity  # 1: Slightly higher activity  # 4: Moderate restlessness  # 7: Severe restlessness |
| **Anxiety** | # 0: No anxiety when resting  # 1: Slight anxiety  # 4: Moderate anxiety at times  # 7: Acute panic attacks |
| **Paroxysmal sweating** | # 0: No sweating  # 1: Almost not detectable, only palms  # 4: Beads of perspiration on the forehead  # 7: Heavy sweating |

**Nursing Delirium Rating Scale = Nu-DESC**

**CAM-ICU**

**
[figure not shown]
**

**Appendix 7:**

**Visual Analog Scala (VAS) / Numerical Rating Scale (NRS)**

- Necessary in all patients who can respond tot he question regarding pain
- Target pain level ≤ 3

| **VAS/NRS** | **Assessment** | **Points** |
| --- | --- | --- |
| Question about pain | No pain up to  maximal imaginable pain | 0 to  10 |
